### Statistical analysis

All analyses will be conducted using SPSS version 19.0 (Statistical Package for Social Sciences, Chicago, IL, USA). A 0.05-significance level will be adopted in all statistical tests.

We will perform a descriptive statistical analysis of organizational (hospitals) and socio-demographic (patients) characteristics in order to assure the comparability of the intervention and control groups. Baseline measures and changes in outcome variables over the study period for each study arm will be presented as means (± SD).

The main outcome decisional conflict is measured at T1 and will be compared between both groups (intervention and control). Multilevel modelling will be carried to take the hierarchical structure of the data into account by specifying random effects at both hospital and patient level. The least square mean proportions will be estimated and compared to assess the effect of the DA on decisional conflict.

The secondary outcomes will also be compared between both groups using multilevel modelling. Some of the secondary measures consist of repeated measures (for example, HRQoL and decisional regret) and will be treated according the appropriate mixed-model approach; that is, repeated measures anova/ancova will be used for outcomes with two time points (decisional regret, treatment satisfaction), and a random coefficient approach will be used for outcomes with three time points (HRQoL) [67]. Observed variation in treatment choice during the trial period will be compared between groups and at level of the individual hospital. For this second comparison, each hospital’s particular historical treatment variation profile (2008 to 2012) will be obtained from the Netherlands Cancer Registry.

Potentially confounding variables (for example, personality, health skills, and age) will be explored for their impact on the primary and secondary outcomes. Missing data and drop-outs will be described.

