### Primary outcomes

Primary outcome is decisional conflict. The decisional conflict scale (DCS) [32, 33] evaluates the level of decisional conflict on five subscales; the feeling of being well-informed; the clarity of values; the feeling of support during the decision-making process; the feeling of uncertainty about best choice; and the effectiveness of the decision. The level of decisional conflict is measured at T1. The DSC is widely accepted and applied as main outcome measure in (PrCa) DA trials [24, 34–36].

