Our trial has defined decisional conflict as primary measure. As previously mentioned, the DCS is a widely accepted and applied measure in DA evaluations. However, the DCS is also subject to some discussion in the literature about its usefulness as outcome measure in DA evaluations [68]. This is mainly due to its limitation to identify a good decision as a person’s underlying sensitivity to uncertainty may not be fully represented in a high or low decisional conflict score. For example, a high score on the DCS could also represent the effort that one takes to be involved in the decision-making process and absorbing all available information and therefore becoming aware of the difficulty of the decision. Although we are aware of this potential limitation of the DCS, we believe decisional conflict represents the best available affective-cognitive outcome measure that captures the uncertainty involved to prostate cancer treatment decision-making. Uncertainty about disease progression, treatment success and side-effect impact are key elements of the decision-making process in prostate cancer care. Preliminary investigations prior to the current study taught us that decisional conflict levels are substantial; we expect that our DA will be able to reduce these levels and that this potential reduction is meaningful. For meaningful interpretation of our effects we also have additional outcome measures available that can support our findings or can indicate bias if present. Many of our secondary measures focus on the decision-making process (knowledge, satisfaction with information provision, decision-making role) rather than the outcome in terms of a ‘good’ or ‘bad’ decision, this ensures that our conclusions on the usefulness of the DA will not solely depend on interpretation of the DCS.

On a broader level, this study will augment the current paucity of information regarding the implementation of DAs in (Dutch) routine clinical practice, its impact on the treatment decision-making process and long-term effects. This will help patients and clinicians to establish optimal patient-treatment fit. As we hypothesized the effects could involve improved patient involvement and knowledge resulting in higher decision and treatment satisfaction and ultimately reduce regret and improve quality of life.

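### The primary effect is stated as a comparison of proportions, although decisional conflict is a scale score with no cut-off and the trial was sized on an effect size of .50

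*Protocol article*

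**What the plan says.** All references are to the protocol article.

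- **Primary outcomes** names one outcome, "Primary outcome is decisional conflict", assessed with the DCS, which "evaluates the level of decisional conflict on five subscales". On timing: "The level of decisional conflict is measured at T1". Table 1 agrees, with a single mark under T1.
- **Discussion** treats the outcome as a score, noting that a person's sensitivity to uncertainty "may not be fully represented in a high or low decisional conflict score".
- **Sample size calculation** uses a minimum relevant effect size of .50, power .80, alpha .05, an ICC of 0.01 and 19 clusters of 20 patients. It gives no event rates.
- **Statistical analysis** says in general terms that outcome variables will be summarised as means with SDs. For the primary comparison it plans a multilevel model "by specifying random effects at both hospital and patient level", and then: "The least square mean proportions will be estimated and compared to assess the effect of the DA on decisional conflict".

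**The concern.** A least-squares mean is an adjusted mean from a linear model. A proportion belongs to a binary outcome. The sentence joins the two and applies them to a score, and nowhere does the article say how that score would become binary.

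This is more than detail left to an analysis plan, because it is the article's only statement of what the primary analysis will estimate. An analysis plan that follows it must choose a cut-off. One that departs from it conflicts with the published protocol.

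Three things are at stake. A difference in proportions cannot be judged against the .50 the trial calls clinically relevant. A cut-off not fixed in advance could be chosen after the data are seen. And splitting a score discards information, so power falls.

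**Working it through.** **1. Does anything in the article support a proportion?** Primary outcomes speaks of a level on a five-subscale instrument. The Discussion speaks of a score. Sample size calculation gives an effect size and no rates. Statistical analysis summarises outcomes as means with SDs. No section gives a DCS threshold or a responder definition. Nothing supports a binary form.

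**2. Inputs.** From Sample size calculation: effect size 0.50, ICC 0.01, 20 patients in each of 19 hospitals, alpha .05. From Randomization: the larger arm is the intervention. I take this as 9 control and 10 intervention hospitals, or 180 and 200 patients. Assumptions: two-sided test; .50 is a standardised mean difference (the article does not say SD); normal scores with equal SD; intervention scores 0.50 SD lower.

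**3. The plan's own power, on the mean scale.** Design effect = 1 + (20 − 1) × 0.01 = 1.19.
SE = √[1.19 × (1/180 + 1/200)] = 0.1121 SD.
Power = Φ(0.50/0.1121 − 1.960) = Φ(2.50) = 0.994. With a t distribution on 17 df it is 0.987.
The article states .80, which does not reproduce at ICC 0.01. An ICC of 0.10 would give 0.815. That is a separate matter, and the present point does not depend on it.

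**4. Literal reading: split the score at a cut c**, in control SDs above the control mean. Proportions above the cut are p₁ = 1 − Φ(c) for control and p₂ = 1 − Φ(c + 0.5) for intervention.

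Splitting also lowers the ICC. Under the normal model the binary ICC in an arm is (p₁₁ − p²)/[p(1 − p)], where p₁₁ is the chance that two patients of one hospital both exceed the cut when their scores correlate at 0.01. At the control median this is (2/π) × arcsin(0.01) = 0.0064, so the control design effect is 1 + 19 × 0.0064 = 1.121. The intervention arm has 0.0058 and 1.110.

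Power = Φ[(p₁ − p₂)/SE − 1.960], with SE² = p₁(1 − p₁)·DE₁/180 + p₂(1 − p₂)·DE₂/200.

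For c = 0: SE = √(0.25 × 1.121/180 + 0.3085 × 0.6915 × 1.110/200) = 0.0524. Then 0.1915/0.0524 = 3.66, and Φ(3.66 − 1.96) = 0.955.

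| Cut | Control vs intervention above cut | Difference | Power, ICC 0.01 | Power, ICC 0.10 |
|---|---|---|---|---|
| none (mean difference) | – | 0.50 SD | 99% | 82% |
| control mean | 50.0% vs 30.9% | 19.1 points | 96% | 75% |
| +0.5 SD | 30.9% vs 15.9% | 15.0 points | 91% | 69% |
| +1 SD | 15.9% vs 6.7% | 9.2 points | 78% | 56% |

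The ICC column refers to the score; the binary ICC is derived from it. The 0.10 column is a sensitivity case at the top of the range the article calls common, not the plan's value. Carrying ICC 0.01 over unchanged to the binary outcome would give about 94%, 89% and 74%.

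**5. What the table shows.** One and the same 0.50 SD shift becomes 19.1, 15.0 or 9.2 percentage points depending on a cut the article does not give. A proportion difference therefore has no fixed relation to the .50 threshold.

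**The case against.** The strongest reply is that this is one wrong word. Everything around it points to a mean: the score, the effect size without rates, the summaries as means with SDs, and the term least-squares mean itself. On that reading nobody intends to dichotomise and no power is lost. I accept this as the likeliest intention. It does not remove the point, because the sentence that defines the primary result still says something else.

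It is also fair that the power loss is small at the planned ICC. Two of the three cuts stay above .80 and the third falls just below it.

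Two stronger readings are tempting, and the article does not support them.

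- *The model cannot be fitted.* With one value per patient, a patient random intercept on top of a residual could not be estimated. But "specifying random effects at both hospital and patient level" can equally describe an ordinary two-level model in which the patient-level term is the residual. That model is sound.
- *There are five primary tests.* A reader might combine the five subscales with "A 0.05-significance level will be adopted in all statistical tests" and infer a family-wise error of 1 − 0.95⁵ = 22.6%. The article names one primary outcome in the singular and nowhere plans primary tests by subscale. The figure also assumes independent tests, which subscales of one instrument are unlikely to be. Leaving the choice of total score to a fuller document is ordinary for an article.

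**Conclusion.** The point holds for the effect measure alone. The primary effect is wrongly stated: a comparison of proportions is announced for a score that has no binary definition, in a trial sized on an effect size of .50.

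If the wording is a slip, the correction is editorial but still needed, since no other sentence says what is estimated. If it were followed literally, the primary estimate would depend on an unstated cut-off and could not be read against .50. Power would fall from about 99% to roughly 96%, 91% or 78% at the planned ICC. Those figures rest on normal scores, a 0.50 SD shift, a two-sided test, 380 patients split 180 to 200, and a standardised-mean-difference reading of .50. The case for correction does not rest on them.

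**What to change.** Replace the sentence with wording such as:

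> *Adjusted (least-squares) mean DCS total scores at T1 in each arm, and their difference with a 95% CI, will be obtained from a linear mixed model with a hospital-level random intercept and a patient-level residual. The difference will also be given in SD units for comparison with 0.50. The five subscale scores will be reported as secondary.*

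Naming the total score is my assumption about what is meant; the sponsor should confirm it. Stating the random intercept and residual outright also removes any doubt about the patient-level term.

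The cost is one sentence, with no change to data collection or sample size. Trial status says recruitment is under way, so the correction can be recorded, with its date, before the primary outcome is analysed.

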**Methods/design:**

Nineteen Dutch hospitals are included in a pragmatic, cluster randomized controlled trial, with an intervention and a control arm. In the intervention group, the DA will be offered after diagnosis, and a summary of the patients’ preferences, which were identified with the DA, can be discussed by the patient and his clinician during later consultation. Patients in the control group will receive information and decisional support as usual. Results from both groups on decisional conflict, treatment choice and the experience with involvement in the decision-making process are compared. Patients are requested to fill in questionnaires after treatment decision-making but before treatment is started, and 6 and 12 months later. This will allow the development of treatment satisfaction, decisional regret, and quality of life to be monitored. Clinicians from both groups will evaluate their practice of information provision and decisional support.

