## Methods/design

### Objectives and hypothesis

The main objective of this study is to investigate the impact of the DA on shared decision-making and treatment choice. It is hypothesized that DA usage will improve prostate cancer knowledge and satisfaction with information provision and therefore better prepare patients for clinical encounters and the following decision-making, which will result in lower levels of decisional conflict compared to standard care. Further, it is expected that better knowledge and less decisional conflict will also result in improved treatment satisfaction, less regret and, ultimately, improved health-related quality of life (HRQoL). In terms of actual choice, we expect less variation in selected treatments in the intervention group compared to the control group.

A secondary aim is to investigate optimal implementation, as previous studies have emphasized the need to gain more insight on this matter [21]. From the patient perspective, it is expected that some subgroups will experience more benefit from DA usage than others. To identify these groups, the moderating role of age, preferred role in the decision-making process, specific health skills (for example, health numeracy and literacy) and personality on the main outcomes will be investigated. Healthcare providers in the intervention group will be asked their opinion about implementation of the DA. This will be compared with an evaluation of information provision and decisional support as provided by healthcare providers in the control group.

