### Intervention

After being diagnosed with prostate cancer, but before a treatment decision has been made, patients in the intervention arm receive access to the online DA. Healthcare providers are instructed to introduce the DA and the study at diagnosis. However, the pragmatic nature of this trial allows hospitals to integrate the introduction of the DA with their standard information provision routines if that follows later due to follow-up diagnostics or an additional consultation with (oncology) nurses. In daily practice, this means that either the urologist or the (oncology) nurse introduces the DA to the patient. To use the DA, patients receive a card from their urologist stating their relevant disease characteristics (PSA, Gleason, and eligible treatment options) and a personal username and password to gain online access to the DA. If a nurse introduces the DA and accompanying access card, the urologist should provide the requested clinical characteristics to the nurse, either by filling in the card or by leaving a note in the patients’ record.

The DA offers a stepwise guidance through the decision process. In the first step, general information about prostate cancer is provided. The second step offers the consideration between active surveillance and curative treatment (surgery or radiotherapy). Values clarification statements are presented in this step to elicit a patient’s preference based on three main differences between AS and curative treatment; acceptance of deferring treatment (*‘I am confident enough that I will be treated on time*, *if necessary’* versus ‘*I do not want to postpone treatment because I do not want to be too late*’), avoiding possibly unnecessary treatment (‘*If treatment might be unnecessary, I would rather wait*’ versus ‘*I prefer treatment, even if it might be unnecessary*’) and the acceptance of treatment side effects (*‘I find possible treatment side effects like erectile and urinary dysfunctions difficult to accept’* versus ‘*I find the possible treatment side effects acceptable’*). Each statement is related to one of the two offered treatment alternatives in this step. On a slider scale, patients can indicate for each set of statements the strength of their preference towards one of the alternatives.

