For all logistics involved to distributing and processing the questionnaires, the PROFILES-application will be used. ‘Patient Reported Outcomes Following Initial treatment and Long term Evaluation of Survivorship (PROFILES)’ is a registry for the study of the physical and psychosocial impact of cancer and its treatment from a dynamic, growing population-based cohort of both short and long-term cancer survivors. PROFILES was developed in 2009 by a joint research group from Tilburg University and Comprehensive Cancer Centre South (CCCS) with a grant from the Netherlands Organization for Scientific Research (NWO) [31]. PROFILES enables data collection management, from inviting patients to participate in studies to collecting patient-reported outcomes data via web-based or mailed questionnaires, and provides a supporting helpdesk. Patients can send their informed consent form, which they receive with the information letter to PROFILES. On the informed consent form patients can indicate whether they want to receive questionnaires via email or regular mail. Approximately 1 to 2 weeks after treatment decision-making (T1) patients receive either the invitation (email) to fill in an online questionnaire or a paper version at their home address. In the case of a paper version, a stamped self-addressed envelope is provided to the patient to return the questionnaire. If patients do not fill in their questionnaires within two weeks, a reminder letter or email will be send. Patients will be assured that nonparticipation does not result in differential follow-up care or treatment. The PROFILES-application allows for managing the follow-up questionnaires, which are sent at 6 and 12 months following T1.

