### Other measures

Table 2 shows an overview of the other measures. Decision aid users are asked to evaluate the DA by indicating for 25 statements if it applies to the responder or not. The first 11 statements are formulated negatively (for example, ‘I found the decision aid too difficult’), followed by 14 positively formulated statements (for example, ‘I found the decision aid pleasant to use’). Although literature reports positive effects from the usage of DAs in general [47], there may be subgroups that will not benefit from DA-usage. To identify these subgroups, additional measures on (health) skills and personality are included. Objective measures for health literacy and health numeracy are used, with the HRS Experimental numeracy module [48] and the STOHFLA-brief [49], respectively. The Decision Self-Efficacy Scale is used as a subjective measure of the perceived ability to make a decision [50].

**Table 2 Tab2:** Other measures

Measures	Instrument	T1	T2	T3
Implementation (intervention only)				
DA-Acceptability	Self-developed	X		
(health) skills				
Self-efficacy	Decision self-efficacy scale	X		
Health numeracy	HRS Experimental numeracy module		X	
Health literacy	STOHFLA-brief		X	
Psychosocial variables				
Anxiety and depression	HADS, PC-max	X	X	X
Personality	LOT-R, BFI-10	X		
Information seeking preferences	API, NFC-short, Maximization scale	X		
Sociodemographics and other healthcare utilization		X	X	X

Comparable to health skills, the relation of personality to beneficial DA-usage will be investigated. Some studies suggest a link between personality and treatment choice [51, 52]. Following these studies, some relevant aspects of personality will be taken into account: hospital anxiety and depression (HADS-scale) [53], prostate specific anxiety (MAX-PC) [54, 55], optimism (Life Orientation Test - Revised) [56], the big five personality dimensions (Big Five Inventory-10) [57], information seeking preferences (subscale from the Autonomy preference index) [58] and maximization tendencies (Maximization scale) [59].

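### Decision self-efficacy, anxiety and preferred role are cast as moderators or potential confounders although they are measured only after the decision aid, which could change them

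*Protocol article*

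**What the plan says.** **Timing.** The Intervention section states that "before a treatment decision has been made, patients in the intervention arm receive access to the online DA". The first questionnaire comes later. Recruitment says: "Approximately 1 to 2 weeks after treatment decision-making (T1) patients receive either the invitation (email) to fill in an online questionnaire". The abstract gives the full schedule: "Patients are requested to fill in questionnaires after treatment decision-making but before treatment is started, and 6 and 12 months later". Tables 1 and 2 have columns for T1, T2 and T3 only.

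**Roles.** The objectives plan to study "the moderating role of age, preferred role in the decision-making process, specific health skills (for example, health numeracy and literacy) and personality" in order to find the patients who gain more from the DA. The Statistical analysis section adds: "Potentially confounding variables (for example, personality, health skills, and age) will be explored for their impact on the primary and secondary outcomes".

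**What the groups contain.** Table 2 lists the Decision Self-Efficacy Scale (T1) under health skills, with numeracy and literacy (both T2 only). On personality, the text of Other measures says "some relevant aspects of personality will be taken into account: hospital anxiety and depression (HADS-scale") and goes on to prostate-specific anxiety, optimism and the Big Five. Preferred role appears again among the secondary outcomes, and Table 1 schedules decision-making role at T1.

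**Reporting over time.** The Statistical analysis section will present "Baseline measures and changes in outcome variables over the study period for each study arm" as means with SDs.

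**The concern.** A confounder or a moderator has to describe the patient as he was before the intervention. Some of the variables given these roles are first measured after the DA has been used and the decision taken, and they are of a kind that a DA is meant to influence.

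Two things are at stake. First, if the DA effect is adjusted for a variable that the DA itself moved, the part of the effect that runs through that variable is taken out. If the variable and the outcome also share unmeasured causes, a further distortion can enter. Second, a subgroup defined by such a variable does not contain like patients in the two arms. Some DA patients with high self-efficacy may be in that group because the DA put them there, and the control arm has no counterpart to them. Moderation of that kind cannot answer the stated secondary aim of finding out who benefits.

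**Working it through.** The plan gives no figure on this point, so there is none to reproduce. The check is first one of timing and role, then an illustration of size.

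**Step 1: timing against role.**

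| Variable | Measured | Role in the article | Could the DA change it? |
|---|---|---|---|
| Age | Questionnaire item | Moderator, potential confounder | No |
| Decision self-efficacy | T1 | Both, through health skills (Table 2) | Yes |
| HADS, prostate-specific anxiety | T1, T2, T3 | Both, through personality (Other measures) | Yes |
| Preferred role | T1 | Moderator and secondary outcome | Yes |
| Numeracy, literacy | T2 only | Both, through health skills | Unlikely |
| Big Five, optimism | T1 | Both, through personality | Unlikely |

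The three entries marked yes follow from the article's own reasoning:
- The objectives expect the DA to prepare patients better for decision-making, and self-efficacy is described as the perceived ability to decide.
- The Background links active surveillance to anxiety, and the objectives expect the DA to affect treatment choice. Anxiety after the decision can therefore be a consequence of the DA.
- Preferred role is itself listed as an outcome of the trial.

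**Step 2: what adjustment would do.** Let the DA shift the covariate by *a* SD, and let one SD of the covariate go with *b* SD of decisional conflict. Adjustment then removes *a* × *b* from the arm effect. The documents give neither value. The assumed ranges are *a* = 0.2 to 0.4 and *b* = 0.3 to 0.6 in absolute size. The yardstick is the effect size of 0.50 in the Sample size calculation.

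- Low end: 0.2 × 0.3 = 0.06 SD; 0.06 / 0.50 = 12%.
- High end: 0.4 × 0.6 = 0.24 SD; 0.24 / 0.50 = 48%.
- No shift: 0 × *b* = 0, so nothing is removed.

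A simulation with 19 hospitals of 20 patients, ICC 0.01, a true total effect of −0.50 SD and 1,000 runs per setting gave these adjusted arm effects:

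| *a* | *b* | No shared cause | Unmeasured shared cause |
|---|---|---|---|
| 0 | −0.3 | −0.50 | −0.50 |
| 0 | −0.5 | −0.50 | −0.49 |
| 0.2 | −0.3 | −0.44 | −0.46 |
| 0.2 | −0.5 | −0.41 | −0.42 |
| 0.4 | −0.3 | −0.38 | −0.42 |
| 0.4 | −0.5 | −0.30 | −0.34 |

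The unadjusted effect stayed at about −0.50 throughout. The largest loss here is (0.50 − 0.30) / 0.50 = 40%; the 48% above needs *b* = 0.6.

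**Step 3: skills measured at T2 only.** Decisional conflict is measured at T1. Moderation by numeracy or literacy can use only patients who still respond at T2. The planned 25% attrition covers T1 to T3, so it is an upper bound for the loss by T2. This is a missing-data limit, not an effect of the DA on the trait.

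**Step 4: change over time.** No patient-reported value of the repeated outcomes exists before T1. For quality of life, the doctor-patient relationship and acceptance of health status, change from T1 therefore leaves out any DA effect already present at T1. Decisional regret, treatment satisfaction and side-effect impact have no T1 value, so this does not apply to them.

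**The case against.** The strongest reply is that no harmful analysis is actually specified. The main comparison of decisional conflict is a multilevel comparison of the arms with no covariates named. The other variables are only to be explored for their impact on outcomes, and the one adjustment the article spells out, in the Discussion, is conditional and uses hospital-level treatment history. Self-efficacy and anxiety are not named in the sentence on confounders. The objectives illustrate health skills with numeracy and literacy, and Table 2 puts anxiety and depression in a different row from personality. Hospitals were randomised before patients were invited, so differences in patient mix can arise and some adjustment may be reasonable.

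Much of this stands. It protects the primary comparison and shows that the grouping is ambiguous in places. It does not remove the point. Table 2 places self-efficacy under skills, the text places HADS and prostate-specific anxiety under personality, and preferred role is named outright as a moderator while also being an outcome. Finding who benefits is a stated aim. A fuller analysis plan could choose among these variables, but it could not supply values from before the DA.

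A reader might also infer that the article calls T1 the baseline and tests change from it. It does not. T1 is nowhere labelled baseline, the phrase follows a sentence on hospital and socio-demographic characteristics, and changes are only to be presented descriptively. T1 also precedes treatment, so it is a fair pre-treatment reference for quality of life. What remains is the need to say that it is not a pre-DA one.

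**Conclusion.** The point holds for secondary and exploratory work. Decision self-efficacy, HADS, prostate-specific anxiety and preferred role are measured only after the DA, could be changed by it, and are given roles that require pre-intervention variables. Any DA effect adjusted for them could be reduced or distorted, and moderation by them cannot identify the patients who benefit.

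The size is unknown. The 12 to 48% range rests wholly on assumed values of *a* and *b*, and the bias is nil if the DA does not move the covariate. It would be tempting to read that range as a bias in the primary result. The documents do not support this, because no adjusted primary model is stated. Nor does the point apply equally to every listed variable: age is not affected, and for numeracy, literacy, the Big Five and optimism the concern is weak because these are fairly stable traits.

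**What to change.** Reword the Objectives and Statistical analysis sections as follows:

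- Limit any adjustment of the DA effect to variables the DA cannot change: age, education, tumour risk characteristics and the hospital-level randomisation factors.
- Report decision self-efficacy, HADS, prostate-specific anxiety and preferred role as outcomes or mediators, and drop them as confounders and moderators.
- Base the subgroup aim on age, education and stable traits, and label moderation by literacy or numeracy as limited to patients who respond at T2.
- State that T1 is a post-DA, pre-treatment time point. Report arm differences at T1, T2 and T3 for outcomes measured then, and do not read change from T1 as the full DA effect.

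This needs no new data and leaves the primary comparison as it is. The cost is fewer moderator claims; in particular, preferred role and self-efficacy could no longer be used to say who benefits.
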